#### Acceptability of preventive care delivery

Clients will be asked to respond on a five-point Likert scale their agreement with statements regarding each element of care for each health risk behavior (strongly disagree to strongly agree). For example, ‘It is acceptable for the service to ask you about how much alcohol you drink.’ Clients will additionally be asked to respond on a five-point Likert scale their agreement with statements regarding receiving each element of care for all four health risk behaviors in the one appointment (strongly disagree to strongly agree).

### Measures: clinician CATI

#### Clinician characteristics

Clinicians will be asked to report their age (20 to 29, 30 to 39, 40 to 49, 50 to 59, 60 to 64, 65 to 69, 70+), Aboriginality (Aboriginal, Torres Strait Islander, both, neither), years in their current discipline (1 to 2, 3 to 4, 5 to 9, 10+), and their current employment status (full time, part time, casual, other). Clinicians will further be asked to report on their own health behavior risk status during the month prior to the interview. Additional clinician characteristics including service type and discipline type will be obtained through the electronic medical records system.

#### Preventive care delivery

On a scale of 0% to 100%, clinicians will be asked to estimate over the previous two months the proportion of new adult clients they provided with the following:

1. Assessment: the proportion for which they assessed their smoking status, fruit and vegetable intake, alcohol consumption, and physical activity;

2. Brief Advice: For clients with health risk behaviors, the proportion to which they provided brief advice to modify that behavior(s); and

3. Referral: For clients with health risk behavior(s), the proportion they spoke to about the telephone support services, the proportion they arranged for a telephone support service to call them, the proportion they recommended speak to their GP or Aboriginal Medical Service about that behavior(s), the proportion they advised to use any other supports to make changes to their health behavior(s), and the proportion they offered to send a summary of their health risks behavior(s) to their GP or Aboriginal Medical Service.

#### Attitudes and beliefs towards preventive care

Clinicians will be asked to respond on a five-point Likert scale their agreement with a number of statements related to their attitudes and beliefs towards providing preventive care to their clients (strongly disagree to strongly agree). Items will relate to: whether clients find preventive care acceptable, clinician confidence in providing preventive care, availability of services to refer clients to, whether clients will change their behaviors as a result of the care they provide, management support regarding the delivery of preventive care, knowledge and skills, role congruence, time available to provide preventive care, whether preventive care will jeopardize relationships with clients, and whether clients are interested in changing health behaviors.

#### Resources and supports available for preventive care delivery

Clinicians will be asked whether there are resources and supports available to assist in the delivery of preventive care (yes, no, don’t know), and where available, the usefulness of that resource or support (very useful, somewhat useful, not at all useful). Resources and supports will include printed educational materials (*e.g*., hard copy resources), educational meetings (*e.g*., training), local opinion leaders (*e.g*., a staff member to support preventive care), audit and feedback (*e.g*., feedback on preventive care provided within the service), and reminders or prompts (*e.g*., list of referral services).

#### Sample size and power

Pilot data indicate an expected completion rate of 50% for the primary data collection (client CATI). Based on this completion rate, the estimated sample size is as follows: 1,040 participants during the baseline periods (260 from group 1; 780 from group 2), 1,040 participants during the intervention periods (520 from each of group 1 and group 2), and 1,040 participants during the follow-up periods (780 from group 1; 260 from group 2) (see Figure 1).

Based on a 50% prevalence of care at baseline, and with before and after samples of approximately 1,040 clients, the study will have 80% power to detect a 7% increase in the provision of assessment of risk behaviors at the 1.67% significance level. An alpha level of 0.0167 has been chosen because there are three primary endpoints to be tested (assessment for all behaviors, advice for all behaviors, and referral for all behaviors). Analysis of changes in the provision of brief advice or offer of referral will be undertaken only for clients who report a risk factor. Based on the least prevalent risk factor (50% of clients at harm for harmful alcohol consumption), there will be before and after samples of approximately 520 clients at risk. With a presumed prevalence of care at baseline of 50%, the study will have 80% power to detect a 10% increase in the provision of brief advice and offer of a referral.

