#### Client CATI

Logistic regression will be used to examine changes in preventive care delivery from baseline to follow-up, across the two groups combined. The models will examine change in each of the behaviors and change in all four behaviors combined. In the first set of models, the outcome of interest will be the client-reported assessment of risk behavior. The predictor variable of interest will be time (*i.e*., before/after) and we will include the covariates of age, gender, and number of visits to the service in the prior 12 months to account for any introduced selection bias [57] and group.

The second set of models will be restricted to those subjects who report risk behaviors, with the outcomes of interest being whether the community mental health clinician was reported to have provided brief advice or offer of a referral.

As simple random sampling of community mental health clients from a complete list of all clients who attended at least one face-to-face individual appointment with a community mental health clinician within the previous two weeks was used (see Recruitment), there is no need to adjust for clinician, community mental health service, or any other natural clustering that occurs within the community. An unadjusted analysis will provide an unbiased estimate of the statistics of interest.

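### Three primary endpoints at a fixed 0.0167 each is valid control, but Holm's step-down gives the same 5% family-wise control with more power at the same sample size

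*Protocol article*

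**What the plan says.** Under Sample size and power, the protocol article gives the reason for its significance level: "An alpha level of 0.0167 has been chosen because there are three primary endpoints to be tested". The endpoints are "assessment for all behaviors, advice for all behaviors, and referral for all behaviors". The level is 0.05/3 = 0.01667, which rounds to 0.0167.

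The power statements are made at that level. For assessment, the claim is: "with before and after samples of approximately 1,040 clients, the study will have 80% power to detect a 7% increase". The starting rate behind that claim is worded "Based on a 50% prevalence of care at baseline". For advice and referral, the sizing uses the least prevalent risk factor: "there will be before and after samples of approximately 520 clients at risk", and "the study will have 80% power to detect a 10% increase in the provision of brief advice and offer of a referral". The alpha is not restated for this second statement. The client numbers already allow for non-completion ("Pilot data indicate an expected completion rate of 50% for the primary data collection (client CATI").

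The Client CATI part of Statistical analysis describes the logistic models and says "The models will examine change in each of the behaviors and change in all four behaviors combined". It gives no decision rule for combining the three primary tests, so the fixed 0.0167 is the only rule the article states.

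**The concern.** With a fixed level, each endpoint must reach 0.0167 whatever happens to the other two. Once one null hypothesis has been rejected, at most two can still be true, and family-wise 5% no longer requires a level as strict as 0.0167 for the rest. Holm's procedure uses that slack.

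The intervention targets all three care elements together, so the case where two or three effects are real is the one the study hopes for. That is also the case where the fixed split loses power. What is at stake is the chance of showing improvement in all of assessment, advice and referral. The validity of the error control is not in question.

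**Working it through.** **Inputs** (Sample size and power): three primary endpoints; alpha 0.0167 each; assessment 50% to 57% with 1,040 clients before and 1,040 after; advice and referral 50% to 60% with 520 before and 520 after. Sidedness is not stated. The correlation between the three test statistics is not stated either, so 0 to 0.8 is an assumption.

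**1. The plan's own figures.** Two-sided critical value at 0.05/3: 2.394. Power = Φ[(difference − 2.394 × SE0)/SE1], where SE0 is the pooled and SE1 the unpooled standard error.

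- Assessment: SE0 = √(2 × 0.535 × 0.465/1040) = 0.02187 and SE1 = √((0.25 + 0.2451)/1040) = 0.02182. Power = Φ[(0.07 − 0.05236)/0.02182] = Φ(0.81) = 79.1%.
- Advice or referral: SE0 = √(2 × 0.55 × 0.45/520) = 0.03085 and SE1 = √((0.25 + 0.24)/520) = 0.03070. Power = Φ[(0.10 − 0.07386)/0.03070] = Φ(0.85) = 80.3%.

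Both agree with the stated 80% to within about one point. One-sided tests at 0.0167 would give 85.9% and 86.9%, so the plan is two-sided.

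**2. Error control as planned.** Three independent tests at 0.0167: 1 − (1 − 0.0167)³ = 0.0493. Upper bound under any dependence: 3 × 0.0167 = 0.0501, where the excess over 0.05 is rounding. The primary family is controlled.

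**3. Why Holm never rejects less.** The smallest p-value is compared with 0.05/3, as now. If it is rejected, the next is compared with 0.025, and if that is rejected, the last with 0.05. Every threshold is at least 0.0167, so any p-value rejected by the equal split is rejected by Holm.

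**4. Size of the gain.** Expected z-statistics at the design effects: 0.07/0.02182 = 3.21 for assessment and 0.10/0.03070 = 3.26 for advice and for referral. Three correlated normal z-statistics with these means were simulated (2,000,000 draws per row, two-sided tests). All three effects are real:

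| Correlation (assumed) | Power per endpoint, fixed 0.0167 | Power per endpoint, Holm | All three, fixed 0.0167 | All three, Holm | At least one, either method |
|---|---|---|---|---|---|
| 0 | 79–81% | 87.5–88.4% | 51.5% | 71.9% | 99.2% |
| 0.3 | 79–81% | 86.6–87.5% | 57.3% | 74.6% | 97.2% |
| 0.5 | 79–81% | 86.0–86.9% | 61.4% | 76.9% | 95.1% |
| 0.8 | 79–81% | 84.8–85.6% | 68.8% | 80.8% | 90.0% |

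Check at correlation 0: 0.792 × 0.806 × 0.806 = 0.515.

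**5. Where the gain shrinks.** With two real effects (assessment and one other), power per real endpoint rises from 79–81% to 82–84%. With only assessment real, it goes from 79.2% to 79.3–79.4%, which is practically nothing. The chance of at least one rejection is identical in every setting, because Holm's first step is the same test.

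**6. Error control under Holm.** In the same simulations, with none, one or two effects real, the family-wise error under Holm was at most 0.0493.

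**The case against.** The strongest reply is that a valid, simple method fixed in advance is not a defect. That stands. The 0.0167 is correct arithmetic, it controls the family, and the stated power reproduces at that level. The equal split also has a real convenience: each endpoint gets its own interval at the matching level without further work. It is also fair to say that 0.0167 appears only in the sample size section, and that a Holm design would be sized at the same level. But the article states no step-down, and its wording reads naturally as a fixed level per endpoint. One sentence removes the doubt.

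A reader might infer something stronger: that the models for each behaviour within each care element are further confirmatory tests outside any error control, since the Client CATI analysis section lists them beside the combined models without ranking them. The document does not support that. The primary endpoints are defined over all behaviours. The behaviour-specific models are nowhere called primary, so they need not share the primary alpha. Nothing says they would be reported as confirmatory. How secondary models are ranked is ordinary SAP content, and the SAP is not shown. Nor does sizing advice and referral on clients at risk from alcohol make alcohol a separate confirmatory endpoint. The article uses the least prevalent risk factor as a cautious floor for the number at risk.

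**Conclusion.** The plan's control of the three primary endpoints is valid but not the most efficient available. At the design effects, Holm adds roughly 5 to 8 percentage points of power per endpoint and 12 to 20 points for showing all three.

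These figures rest on four assumptions: two-sided tests; all three effects real at the stated sizes; the stated client numbers, including 520 at risk for both advice and referral; and a correlation of 0 to 0.8 that the article does not give. They use the simple before/after comparison on which the article's own power is based, with no covariate adjustment. The point is minor: a cheap improvement that leaves the sample size unchanged.

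**What to change.** In the Client CATI analysis section, state that the three primary p-values will be tested by Holm's step-down procedure at a two-sided family-wise 5%. Keep 0.0167 in Sample size and power, since it is still the level of the first step. The cost is one sentence and no new data. The only downside is that simultaneous intervals matching Holm are less simple than the 98.33% intervals (1 − 0.05/3) that match the equal split.

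As an optional clarification, the same section could label the behaviour-specific models as secondary, to be reported with estimates and intervals.

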### Statistical analysis

Descriptive statistics will be used to describe client and clinician characteristics, risk status, prevalence of preventive care provided, client acceptability of preventive care, clinician attitudes and beliefs toward preventive care, and clinician-reported availability of resources and supports for preventive care delivery.

#### Client CATI

Logistic regression will be used to examine changes in preventive care delivery from baseline to follow-up, across the two groups combined. The models will examine change in each of the behaviors and change in all four behaviors combined. In the first set of models, the outcome of interest will be the client-reported assessment of risk behavior. The predictor variable of interest will be time (*i.e*., before/after) and we will include the covariates of age, gender, and number of visits to the service in the prior 12 months to account for any introduced selection bias [57] and group.

The second set of models will be restricted to those subjects who report risk behaviors, with the outcomes of interest being whether the community mental health clinician was reported to have provided brief advice or offer of a referral.

As simple random sampling of community mental health clients from a complete list of all clients who attended at least one face-to-face individual appointment with a community mental health clinician within the previous two weeks was used (see Recruitment), there is no need to adjust for clinician, community mental health service, or any other natural clustering that occurs within the community. An unadjusted analysis will provide an unbiased estimate of the statistics of interest.

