#### Clients

Clients eligible for participation in the CATI interviews will be those who: are 18 years or older; have attended at least one face-to-face individual appointment with a community mental health clinician within the previous two weeks; have not previously been selected to participate; and have not been identified by their clinician as inappropriate to contact. Additional client eligibility criteria will be assessed upon phone contact and will include: English speaking; not participating in any other surveys regarding health behaviors or care received at community health services; not living in aged care facilities or jail; and being physically and mentally capable of responding to the survey items.

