### Recruitment

#### Clients

Each week, for 36 months, a random sample of 40 adult clients (20 from each of the two groups) who had received care at the eligible community mental health services in the prior two weeks, will be selected from electronic medical records and invited to participate in the data collection.

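### The complete-list sampling premise conflicts with the rule excluding clients already selected; the resulting drift towards newer clients is confounded with before/after and only partly covered by the visits covariate

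*Protocol article*

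**What the plan says.** The Client CATI part of Statistical analysis describes the sample as "simple random sampling of community mental health clients from a complete list of all clients who attended at least one face-to-face individual appointment" within the previous two weeks. From this it concludes that no adjustment for clinician, service or other clustering is needed and that an unadjusted analysis is unbiased. The paragraphs before it specify logistic regression on time (before/after), with age, gender, visits in the prior 12 months and group as covariates. The first three are included to deal with possible selection bias.

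Participants, Clients, restricts the list to those who "have not previously been selected to participate; and have not been identified by their clinician as inappropriate to contact". Recruitment, Clients, sets the draw: "Each week, for 36 months, a random sample of 40 adult clients (20 from each of the two groups".

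Sample size and power gives the phase sizes: "1,040 participants during the baseline periods (260 from group 1; 780 from group 2" and "1,040 participants during the follow-up periods (780 from group 1; 260 from group 2". The target for the first primary endpoint is that "the study will have 80% power to detect a 7% increase in the provision of assessment of risk behaviors at the 1.67% significance level".

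**The concern.** The list sampled each week is not complete and does not represent the same population throughout. Everyone selected earlier is missing from it, including those who did not complete an interview.

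A client who stays for years appears on many weekly lists and will probably be drawn sooner or later. A newly arrived client has not yet been exposed to any draw. As the study runs, the eligible list therefore shifts from longer-term to newer clients. In each group the whole follow-up period comes after the whole baseline period, so depletion is always further advanced in the after sample. Staggering the groups does not cancel this, because the shift runs the same way in both and the planned model has a before/after term without a concurrent-control contrast.

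If receipt of preventive care differs between newer and longer-term clients, the shift produces a before/after difference with no change in practice.

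**Working it through.** **Reproducing the plan's figures.** Completed interviews are 20 per week × 50% completion × weeks: 26 weeks gives 260, 52 gives 520 and 78 gives 780. Hence 260 + 780 = 1,040 before and 780 + 260 = 1,040 after, as stated. At two-sided alpha 0.0167, 1,040 per period gives 79.1% power for 50% versus 57%, and 520 per period gives 80.3% for 50% versus 60%. Both match the stated 80%. The power calculation is not in question.

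**Removals from the list.** The count is 20 × weeks elapsed, because selection itself excludes, whether or not an interview follows.

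| | Baseline weeks | Removed during baseline | Follow-up weeks | Removed during follow-up |
|---|---|---|---|---|
| Group 1 | 1–26 | 0 to 520 | 79–156 | 1,560 to 3,120 |
| Group 2 | 1–78 | 0 to 1,560 | 131–156 | 2,600 to 3,120 |

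Taking midpoints, the average number removed rises from 260 to 2,340 in group 1 and from 780 to 2,860 in group 2. The increase is 2,080 in each.

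**Shift in composition.** The documents give neither list size nor turnover, so these are assumed. A weekly cohort model starts in steady state with 50% or 80% of listed clients long-stay (mean 5 years) and the rest short-stay (mean 3 months). It compares the share with more than one year in the service, before versus after, within group, on the actual phase windows. Without the exclusion rule the shift is 0. With it:

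| Listed per group | Fall in share over 1 year (50% / 80% long-stay) | × assumed 20-point difference in care |
|---|---|---|
| 1,000 | 31 / 53 points | 6.2 / 10.5 points |
| 2,000 | 23 / 40 | 4.6 / 8.0 |
| 4,000 | 12 / 14 | 2.3 / 2.8 |
| 8,000 | 6 / 6 | 1.1 / 1.2 |

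The 1,000-client, 80% long-stay cell is a limit rather than a realistic case: the eligible list ends at 18, below one weekly draw. For orientation only, about 200 eligible clinicians split evenly would be 100 per group, so 2,000 to 3,000 clients per group would be 20 to 30 per clinician.

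**Effect of the planned visits covariate.** The table makes no covariate adjustment. A second model simulates individual attendance: 1,000, 2,000 or 3,000 continuing clients per group, 50% attending in a given week, with 0.3% weekly turnover; 15 to 20 new clients a week, 70% attending, staying 12 weeks; and the same 20-point difference in care. Fitting before/after and group on the actual windows, with and without a linear visits term, gives:

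| Continuing clients per group | Without visits | With visits |
|---|---|---|
| 1,000 | about 11 points | 0.0 to 1.0 |
| 2,000 | about 5 | 0.3 to 0.9 |
| 3,000 | about 2 | −0.1 to 0.5 |

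Adjustment works well here because the two kinds of client barely overlap on visits. A new client expects at most 12 × 0.7 = 8.4 visits, and a continuing client present all year expects 52 × 0.5 = 26. With less frequent, more uneven or longer attendance the overlap grows. For example, a new client seen weekly for 12 weeks has 12 visits, and a long-term client seen every four weeks has 52 / 4 = 13. Under such patterns the change left after adjustment is about 0.3 to 4 points. Age and gender were not modelled.

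**The case against.** The strongest objection is that the unadjusted figures describe an analysis the trial does not plan. The model includes visits in the prior 12 months, expressly against selection bias, and in the favourable scenario that covariate removes nearly all of the distortion. This stands, and it rules out quoting 2 to 11 points as the expected bias. It does not remove the concern, because visits are a proxy for time in the service and the protection weakens when attendance is sparse or uneven.

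Second, the sign is not known. A reader might infer that the drift must inflate the apparent effect because new clients are asked about risks at intake. The documents do not support that. Intake triage services are excluded, and the client item on assessment states no recall limit, so longer-term clients may have had more occasions on which to be asked. The drift could equally hide a real improvement.

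Third, a reader might take the unbiased statement as a claim to be free of all selection bias. In context it mainly concerns clustering, and the same section separately allows for selection bias. What remains wrong is the premise offered for it.

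Fourth, two other features might be read as adding to the drift. Clinician exclusions also make the list incomplete, but nothing indicates that they change over time. The fixed draw of 20 per group creates no drift, and group is already in the model.

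Finally, an unseen analysis plan might already adjust for time in the service. That would reduce the bias, but the article would still state a sampling premise that its own eligibility rule contradicts.

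**Conclusion.** The contradiction is in the text and needs no assumption: the list is neither complete nor stable, and in both groups depletion is further advanced at follow-up than at baseline. The drift towards newer clients follows from the design. Its effect on the estimate cannot be fixed from the documents.

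With 1,000 to 3,000 continuing clients per group and a 20-point difference in care, all assumed, the spurious change is about 2 to 11 points unadjusted and from under 1 to about 4 points after adjusting for visits. The target is 7 points. It would be smaller with larger lists or a smaller difference in care, and its direction is open.

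A reader might infer that the bias could by itself match the target effect. For the planned, adjusted analysis these calculations do not show that. What they do show is a plausible residual bias that is cheap to reduce.

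**What to change.** - Add time since first contact with the service, or new versus continuing status, from the electronic record as a covariate in both sets of client models.
- As a sensitivity analysis, standardise the before and after prevalences to the tenure and visit profile of all attenders in each period, also from the record. If the list proves small, few longer-term clients may remain at follow-up to carry the weights, so inspect these first.
- Report, by group and period, the list size and the numbers excluded as previously selected or ruled out by a clinician.
- Replace the complete-list wording with the actual scheme, weekly random sampling within group without replacement, and limit the unbiased statement accordingly.

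The cost is one extra field from a record system that already supplies age, gender and visit counts, with negligible loss of precision. That the record holds a first-contact date is assumed. Only the analysis and its description change, so this remains possible although the intervention is already under way in the second group.

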### Participants

#### Community mental health facilities

All community mental health facilities in the health district providing care to adult clients (19 services) will receive the clinical practice change intervention. Community mental health care services provided by such facilities include general adult community mental health services, and specialized community mental health services, including older persons services and psychiatric rehabilitation. Types of community mental health care services excluded from participating in the study will include inpatient and intake triage services, and services providing care solely to clients under the age of 18.

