#### Clinicians

All clinicians within eligible services will receive the intervention. This includes multidisciplinary teams of psychiatrists, psychologists, social workers, dieticians, nurses, and occupational therapists. All clinicians who have had a minimum of 10 individual face-to-face appointments with adult clients within the two months prior to the survey, have been employed for a minimum of three months, and are not contractors are eligible for participation in the CATI interviews.

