#### Clinicians

Clinician surveys will be undertaken pre and post the intervention delivery for each of the two groups. All eligible community mental health clinicians providing care to clients at the community mental health services (approx. n = 200) will be identified through electronic medical records and will be invited to participate in the data collection.

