#### Clinical practice change intervention

The multi-strategic clinical practice change intervention will be implemented at each community mental health service to support the provision of preventive care delivery. The practice change intervention is informed by extensive practice change research and reviews of the clinical practice change literature [29,30,32,33,56] and will include the following:

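### Random sampling of clients does not justify ruling out adjustment for service: if the 19 services change differently between periods, the before/after standard errors are too small

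*Protocol article*

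**What the plan says.** The Client CATI part of the statistical analysis section plans an ordinary logistic regression of care received on period (before or after). The two groups are combined, and the covariates are age, gender, number of visits and group. It then argues from the sampling scheme: "As simple random sampling of community mental health clients from a complete list of all clients who attended at least one face-to-face individual appointment" was used, therefore "there is no need to adjust for clinician, community mental health service, or any other natural clustering that occurs within the community". It adds that the unadjusted analysis gives unbiased estimates.

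Elsewhere the protocol places the intervention above the client. In the Participants section, on which facilities take part, it states: "All community mental health facilities in the health district providing care to adult clients (19 services) will receive the clinical practice change intervention". Under Clinical practice change intervention, it "will be implemented at each community mental health service to support the provision of preventive care delivery". Under Participants, Clinicians: "All clinicians within eligible services will receive the intervention"; the recruitment section puts them at about 200. Most components work through the service or its staff: site consultation, manager training, monthly performance reports discussed with managers, and a support officer for each service.

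The sample size section contains no allowance for clustering.

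**The concern.** The outcome is what clinicians do, as reported by their clients. If one service takes up the intervention faster than another, or drifts for reasons of its own, all its clients in that period move together. That service-by-period variation enters the before/after contrast however the clients were drawn. Sampling clients at random makes them representative of the client list. It does not make their outcomes independent for inference about an intervention effect. Nor does the claim of unbiasedness help, because it concerns the point estimate and not its standard error.

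At stake are the confidence intervals and the significance level of all three primary endpoints. The 1.67% level was chosen to protect against testing three endpoints, and an understated standard error can undo that protection. Because the protocol affirmatively rejects adjustment and gives a reason, this is not a detail left for a later document.

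**Working it through.** **1. The plan's own power.** Inputs from Sample size and power: 1,040 before and 1,040 after, 50% to 57%, alpha 0.0167 (taken as two-sided, z = 2.393). Pooled-variance formula: power = Φ[(d − z·SE0)/SE1]. SE0 = √(2 × 0.535 × 0.465/1,040) = 0.02187 and SE1 = √((0.25 + 0.2451)/1,040) = 0.02182. Power = Φ[(0.07 − 2.393 × 0.02187)/0.02182] = 79.1%. For 50% to 60% with 520 per period, it is 80.3%. The stated 80% therefore reproduces as a calculation for independent observations.

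**2. Group adjustment, a separate matter.** The samples are 260 before and 780 after in group 1, and 780 before and 260 after in group 2. With group in the model, the variance of the change is ½ × 0.25 × (1/260 + 1/780) = 0.25 × 2/780. The effective sample is 780 per period, not 1,040, and power for 7 points is 64.8%. This loss comes before any clustering.

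**3. Design effect on the change.** The documents give no ICC and no between-period correlation of service effects (r), so both are assumed. With 19 equal services (9.5 per group on average), each has 260/9.5 = 27.4 interviews in its smaller period and 780/9.5 = 82.1 in its larger one.

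- Variance of one service's change, relative to σ²: (1 − ICC)(1/27.4 + 1/82.1) + 2·ICC·(1 − r).
- Dividing by (1/27.4 + 1/82.1): DE = (1 − ICC) + h·ICC·(1 − r), with h = 2/(1/27.4 + 1/82.1) = 41.05.
- True type I error of the unadjusted test: 2[1 − Φ(2.393/√DE)].

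| ICC | r | DE | Type I error | Power for 7 points, correctly clustered test, n = 780/DE |
|---|---|---|---|---|
| 0.01 | 0.5 | 1.20 | 2.9% | 56% |
| 0.01 | 0.8 | 1.07 | 2.1% | 61% |
| 0.01 | 0.9 | 1.03 | 1.8% | 63% |
| 0.02 | 0.5 | 1.39 | 4.2% | 48% |
| 0.02 | 0.8 | 1.14 | 2.5% | 58% |
| 0.02 | 0.9 | 1.06 | 2.0% | 62% |
| 0.05 | 0.5 | 1.98 | 8.9% | 34% |
| 0.05 | 0.8 | 1.36 | 4.0% | 49% |
| 0.05 | 0.9 | 1.16 | 2.6% | 57% |
| 0.01–0.05 | 1 | 0.99–0.95 | 1.6%–1.4% | 65%–67% |

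The power column has no small-sample correction.

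**4. Check by simulation.** A group-stratified before/after comparison was simulated with 10 and 9 services assumed and 20,000 runs per setting. The ratio of true to model standard error was 1.11 at ICC 0.01, r 0.5 (type I error 3.1%), 1.18 at ICC 0.05, r 0.8 (4.6%) and 1.42 at ICC 0.05, r 0.5 (9.3%). The formula gives √DE = 1.09, 1.17 and 1.41. With r = 1 the ratio was 1.00 and type I error about 1.7%.

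**5. Advice and referral.** At the planned 520 per period, h halves to 20.5. Over the same grid DE runs from 0.99 + 20.5 × 0.01 × 0.1 = 1.01 to 0.95 + 20.5 × 0.05 × 0.5 = 1.46, and type I error from 1.7% to 4.8%.

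**The case against.** The best defence concerns the target. The protocol defines effectiveness as a rise in the prevalence of clients reporting care in these services, and all 19 adult services of the district are included, so services are a census and not a sample. For the change in prevalence among this district's clients in these exact periods, random client sampling does support an unclustered variance, and the policy remarks in the Discussion do not formally define a wider population. This stands as far as it goes. But it describes what happened in the district. Attributing the change to the intervention also needs allowance for how much services shift between periods on their own, and client sampling says nothing about that.

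The second objection concerns size, and it stands. A reader might infer that the planned standard errors are certainly too small, or apply the full factor 1 + (m − 1)·ICC. The documents support neither. The same services appear before and after, so constant differences cancel, and if every service changed equally (r = 1) there would be no understatement. The 8.9% needs the corner ICC 0.05 with r = 0.5; at ICC 0.01 to 0.02 and r 0.8 to 0.9 the error is 1.8% to 2.5%. Equal change across 19 services is, however, an assumption that the plan neither states nor tests.

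Third, the low power figures should not all be charged to clustering: group imbalance alone gives about 65%. The roughly 50% at ICC 0.05 and r = 0.8 belongs to a correctly clustered test. The unadjusted test planned would keep about 63% there, Φ[(0.07/0.0252 − 2.393)/√1.36], but at a true level of 4.0%.

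**Conclusion.** The statement is wrong as a justification: simple random sampling of clients does not remove the need to consider clustering by service when estimating the effect of an intervention delivered through services. The consequence is conditional. If services change differently between periods, the unadjusted standard errors are too small and the 1.67% level is not held. Under the assumed 19 equal services, ICC 0.01 to 0.05 and r 0.5 to 0.9, the design effect is 1.03 to 1.98 and type I error 1.8% to 8.9% for assessment, with milder figures for advice and referral. None of these inputs can be settled from the documents. It should not be inferred that the point estimate is biased by ignoring service; the issue is its precision. The sentence governs the primary analysis and should be corrected before analysis.

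**What to change.** Delete the statement that no clustering adjustment is needed, then do one of the following:

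- Keep the marginal logistic model and use service-clustered standard errors (GEE or robust) with a small-sample correction for 19 clusters.
- Fit a mixed logistic model with service and service-by-phase effects, noting that its odds ratio is conditional on service and so differs in meaning from the marginal one.

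Report the estimated ICC, and restate power over an assumed range of ICC and between-period correlation.

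No new interviews should be needed, since clients are drawn from the services' electronic records. The statistical cost is real. With a t reference on 17 degrees of freedom (an assumption: 19 services less 2), the critical value rises from 2.393 to 2.654, equivalent to a variance factor of (2.654/2.393)² = 1.23. Power for 7 points then falls from about 65% to Φ(0.07/0.0252 − 2.654) = about 55% even if there is no clustering. At ICC 0.05 and r = 0.8 with this correction it would be about Φ(2.778/√1.36 − 2.654) = 39%. These figures should be disclosed when power is restated.

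The change does not address confounding: an event that coincides with a phase, such as a local initiative, stays in the before/after contrast whichever standard error is used.
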